# PATIENT POPULATION

# This study will prospectively enrol 3,000 patients undergoing CAVI. Sites participating in the CAVI-J of the study will be selected based on data quality and quantity of CAVI.

1. **ELIGIBILITY**

**Patient Eligibility and Screening.**

Patients who have presented or are presenting at a clinic or a hospital for clinical indication — and who meet the inclusion criteria and none of the exclusion criteria — will be included into CAVI-J study.

## Enrollment.

3,000 subjects will be enrolled, with no more than 20% of the total study population enrolled per site. Consecutive consenting adult patients who meet the inclusion criteria and none of the exclusion criteria will be asked to participate in the study.

## Ethical Considerations.

The study will be approved by the ethics committees of all hospitals involved. All participants provided written informed consent before enrollment. This study is conducted according to the principles expressed in the Declaration of Helsinki and is registered at ClinicalTrials.gov (NCT01859897).

**Informed Consent**

Study-specific data collection cannot be started until the patient has met all clinical inclusion criteria and written informed consent has been obtained. The investigator, or a person designated by the investigator who has been trained on the Investigational Plan, will explain the nature and scope of the study, potential risks and benefits of participation, and answer questions from the patient. If the patient agrees to participate, the informed consent form must be signed and personally dated prior to enrollment by the patient or his/her legally authorized representative and the investigator or a person designated by the investigator. A copy of the fully executed informed consent form must be provided to the patient. All patients must provide written informed consent in accordance with the ethics committee.

**Inclusion Criteria:**

patients between 40 and 74 years of age who have at least one of the following

1.Type 2 diabetes mellitus

2.Metabolic syndrome

3.Hypertension categorized as high-risk ^c)^

4.Chronic kidney disease (stage 3) ^d)^

5.History of coronary artery disease or cerebral infarction ^e)^

**Exclusion Criteria:**

1.Under 40 years of age or over 75 years of age

2.Ankle brachial index < 0.9

3.Chronic atrial fibrillation

4.Heart failure (NYHA class III or IV) or left ventricular dysfunction (EF below 40%)

5.Medical history of cancer and/or treatment for cancer within the last 5 years

6.Estimated glomerular filtration rate <30 ml/min/1.73m^2^

7.Chronic hemodialysis

8.Treatment with systemic steroids or immunosuppressants

9.Liver cirrhosis

10.History of PCI/CABG within 6months

11.Severe valvular stenosis or regurgitation

12.Determined as unsuitable for this study by a physician

**Definition of inclusion criteria**

**Type 2 diabetes mellitus:** Diabetes mellitus was defined according to the American Diabetes Association. [20]

**Metabolic syndrome:** Metabolic syndrome was defined with the modified criteria of the Japanese Expert Committee on the Diagnosis and Classification of Metabolic Syndrome for the clinical diagnosis of metabolic syndrome. [8] Waist circumference > 85cm (men) or > 90cm and at least two of following additional risks: fasting glucose > 110mg/dL, triglyceride > 150 mg/dL or HDL < 40mg/dL, and systolic blood pressure > 130mmHg or diastolic blood pressure > 85mmHg.

**Hypertension categorized as high-risk:** Hypertension categorized as high-risk was defined as a complication of diabetes mellitus or chronic kidney disease, or organ damages or multiple risk factors according to the guidelines of the Japanese Society for Hypertension 2009. [21]

[figure not shown]

[figure not shown]

**Chronic kidney disease (stage 3):** Chronic kidney disease (stage 3) was defined as including patients with estimated glomerular filtration rates from 30 to 60 mL/min/1.73 m^2^ in accordance with clinical practice guidebook for diagnosis and treatment of chronic kidney disease 2012 [22]

**History of coronary artery disease or cerebral infarction:** History of coronary artery disease was defined as condition over 6 months after percutaneous coronary intervention or coronary artery bypass surgery. Coronary artery disease included angina pectoris, myocardial infarction, and unstable angina. Non-cardiogenic cerebral infarction is defined as cerebral infarction with an evidence by imaging modality (CT and MRI) except for cardioembolic infarction and intracerebral hemorrhage.

**Patient Discontinuation**

Every subject should remain in the study until completion of the required study period. However, a subject’s participation in any Clinical Investigation is voluntary and the subject has the right to withdraw at any time without penalty or loss of benefit.

**8. STUDY DURATION**

The anticipated duration of this study will be 6 years. Qualifying patients will be enrolled in the study for the first 1 years, and followed for an additional 5 years through follow up visits and/or phone calls.

| Activity | Start Day | Finish Day | Comments |
| --- | --- | --- | --- |
| **Site activation** | June 2013 |  |  |
| **Subject enrollment** | June 2013 | December 2014 |  |
| **Data monitoring** | June 2013 | May 2019 | Simultaneous with enrollment and follow up |
| **Data analysis** | December 2019 | --- |  |
| Abstracts / Publications | February 2020 | --- |  |

**9. DATA COLLECTION**

The following data will be collected:

|  | **Enrollment/Baseline** | **Year 1-5** |
| --- | --- | --- |
| Inclusion and Exclusion Criteria | **x** |  |
| CAVI | **x** | **x**** |
| Clinical Presentation | **x** |  |
| Demographics | **x** |  |
| CAD Risk Factors | **x** |  |
| Other Medical Conditions | **x** |  |
| Height and Weight | **x** |  |
| Laboratory Tests* | **x** |  |
| Medications | **x** |  |
| Drinking habit/physical activity |  |  |
| Primary and secondary outcomes | **x** | **x** |

* Laboratory test must be performed at same date of CAVI. ** Annual measurement of CAVI is not mandatory.

## 10. STUDY-SPECIFIC VARIABLES

Data dictionaries and case report forms will be provided to study investigators. These will include:

### Baseline Data and Laboratory Assessments

### Laboratory assessment and collection will be in accordance with standard hospital policy. In addition, the following assessments will be collected:

- Creatinine
- Total cholesterol
- HDL-C
- Triglycerides
- HbA1c
- Uric acid
- Urine protein (semi-quantitative)

Electrocardiogram

### Medical History and Clinical Presentation

**Demographics:**

- Age
- Sex
- Weight
- Height
- Weight circumflex
- Blood pressure
- Heart rate

**History of CAD:**

- Myocardial infarction
- Percutaneous coronary intervention
- Coronary artery bypass graft

**History of ischemic stroke**

**Concomitant medications:**

- Lipid-lowering agents – statins, ezetimibe, omega-3 fatty acid, etc.
- Antiplatelet therapy – aspirin, P2Y12-inhibitors
- Oral anti-coagulants – warfarin, DOACs
- Anti-hypertensive agents
- Diabetic agents – metformin, SGLT2 inhibitor, insulin, etc.
- Anti-osteoporosis agents

**CAD Risk Factors:**

- Diabetes mellitus
- Hypertension
- Dyslipidemia
- Smoking
- Atrial fibrillation
- Peripheral arterial disease
- Sleep apnea syndrome
- Chronic kidney disease
- Family history of diabetes, hypertension, and cardiovascular diseases

**Drinking habits:** how many times per week, how much volume per once converted as alcohol

**Physical activity:**

Moderate physical activity (>150 minutes per week), vigorous physical activity (> 75 minutes per week) or no physical activity (< 75 minutes per week) will be recorded [23].

**CAVI measurements:**

CAVI was measured using a CAVI device (Vasera; Fukuda Denshi, Tokyo, Japan). Electrocardiogram electrodes were placed on both wrists, a microphone for detecting heart sounds was placed on the sternum, and cuffs were applied to the upper arms and ankles bilaterally with the patient lying supine and the head held in the midline position. The examinations were performed after resting for 10 minutes. The pressure of all cuffs was kept low at 50 mmHg to minimize the effect of cuff pressure on hemodynamics. Blood pressure was then measured. Pulse wave velocity (PWV) was to be obtained by dividing vascular length by the time (T) taken for the pulse wave to travel from the aortic valve to the ankle. However, in practice T was difficult to obtain because the time the blood left the aortic valve was difficult to identify from the sound of the valve opening. Thus, because the time between the sound of the aortic valve closing and the notch of the brachial pulse wave is theoretically equal to the time between the sound of the aortic valve opening and the rise of the brachial pulse wave, T was obtained by adding the time between the sound of the aortic valve closing and the notch of the brachial pulse wave and the time between the rise of the brachial pulse wave and rise of the ankle pulse wave. CAVI was determined using the following formula: CAVI=a{(2ρ/∆P)×ln(Ps/Pd)PWV^2^}+b, where a and b are constants, ρ is blood density, ∆P is Ps–Pd, Ps is systolic blood pressure, and Pd is diastolic blood pressure.

# 11. DATA HANDLING AND RECORD KEEPING

The CAVI-J office will perform data management activities including documentation of the systems and procedures to be used. All e case report form (CRF) data collection will be performed through a secure web portal and all authorized personnel with access to the electronic data capture (EDC) system must use an electronic signature access method to enter, review or correct data. Passwords and electronic signatures will be strictly confidential.

The data will be subjected to consistency and validation checks within the EDC system. Completed eCRF images with the date-and-time stamped electronic audit trail indicating the user, the data entered, and any reason for change (if applicable) will be archived at the Investigator’s site and a backup copy archived with the CAVI-J office.

**Electronic Case Report Form Completion.**

Primary data collection based on source-documented hospital and/or clinic chart reviews will be performed clearly and accurately by the clinical site personnel trained on the protocol and eCRF completion. eCRF data will be collected for all patients that are registered into the study.

**Record Retention.**

The sponsor will archive and retain all documents pertaining to the study for the time of the study under evaluation, and for lifetime during the post-study phase. The Investigator must obtain permission from Executive Steering Committee (ESC) in writing before destroying or transferring control of any study investigation records.

**Publication Policy.**

All publications and other public disclosures related to the Study shall be by the decision of the ESC, in cooperation with the study investigators and clinical site. All publications or other disclosures must be approved in advance by the ESC.

Study investigators may use all study-related data for the purposes of scientific investigations, scientific abstracts, and scientific publications as has been approved by the ESC.

The CAVI-J office will be responsible for registering the study on clinicaltrials.gov, or any other clinical investigations, in accordance with the International Committee of Medical Journal Editors guidelines, or any other applicable guidelines.

# 12. STUDY ORGANIZATION

**Study Investigators.**

The Investigator(s) undertake(s) to perform CAVI-J in accordance with this protocol, ICH guidelines for Good Clinical Practice and the applicable regulatory local requirements.

The Investigator is required to ensure compliance with all procedures required by this protocol. The Investigator agrees to provide reliable data and all images into the EDC system in an accurate and timely fashion. The Investigator may appoint such other individuals as he/she may deem appropriate as Sub-Investigators to assist in the conduct of the study. All Sub-Investigators shall be appointed and listed. The Sub-Investigators will be supervised by and under the responsibility of the Investigator. The Investigator will provide them with a CAVI-J Protocol and all necessary information to successfully perform the study.

**Data Coordinating Center (DCC).**

As the DCC, CAVI-J office bears responsibility for monitoring interim data and analyzing the study's results in conjunction with the Investigators. Issues relating to regulatory reporting are the responsibility of both the Investigator and the DCC will aim to support these activities. The DCC will coordinate and monitor the study activities in alliance with the Principal Investigators, the ESC, and the sub-committees.

**Organizational and Leadership Design.**

The CAVI-J study organizational structure will comprise a study chair, principal investigators, an ESC; as well as dedicated disease-specific sub-committees.

**Study Chairs.**

The Study Chair will be responsible for the overall leadership of the study. The Study Chairs will work with site investigators and subcommittees, and will be responsible for reporting any pertinent findings to the ESC.

The Study Chair will be:

[name]

**Principal Investigators.**

Principal Investigators will be from investigative sites.

**Executive Steering Committee.**

The ESC is charge with the responsibility for ensuring scientific quality and study fairness. It is composed of the Study Chair, Principal Investigators, and Site Investigators. The ESC will meet at once a year to review study progress and conduct. The ESC will provide feedback to the CAVI-J office and study investigators after each meeting and on an *ad hoc* basis. In that capacity, The ESC will address and resolve scientific issues encountered during the course of the study. All final decisions regarding trial or protocol modifications rest with the ESC.

All proposed research investigations for CAVI-J study must be approved by the ESC.

The ESC membership will be comprised of the following (in alphabetical order):

1. [name]
2. [name]
3. [name]
4. [name]

**Clinical Endpoint Review Committee**

The Clinical Endpoint Review Committee (CEC), consisting of members blinded to information about the patients, will assess the appropriateness of the clinical judgment of the cardiovascular events according to prespecified criteria.

The CEC membership will be comprised of the following:

1. [name]
2. [name]
3. [name]

**13. Quality Control and Assurance**

**Site Qualification.**

Each clinical center will be required to obtain ethics committee approval for the protocol and consent (and their revisions) in a timely fashion, to recruit patients, to collect data and enter it accurately in the EDC system, to faithfully follow the protocol and adhere to the standards of Good Clinical Practice (GCP). Each participating site contributing patient-level data to CAVI-J study should meet the following site requirements:

- ability to organize data required for completion of CAVI-J case report form
- ability to perform de-identification of Protection Health Information (PHI) securely on-site in a manner in keeping with local regulations

**Investigator Profile.**

The following information will be collected for all investigators who participate in the study: CVs, contact information including address, telephone, and email, Conflict of Interest Statement and Financial Disclosure Certifications prior to initiation of enrollment.

**Qualifications and Training.**

Clinical investigators will be cardiology investigators with expertise in vascular function test including CAVI.

All clinical site investigators and coordinators will be trained by the DCC in the specifics of the protocol during site initiation in advance of patient enrollment. In addition, the investigators and coordinators will undergo a separate training session to gain familiarity with the EDC system.

**Safety Monitoring.**

Study Investigators and their site designees will be responsible for monitoring safety data throughout the course of the study.

**Delegation of Authority and PI Oversight.**

Principal Investigators are responsible for all study activities at their sites. They may delegate study tasks to qualified staff members while continuing to oversee all study activities. The Delegation of Authority Log will list each staff member’s title and responsibilities for the study. The PI is responsible for careful review of each staff member’s qualifications.

**Site Approval.**

The following documents must be collected prior to site approval and opening to patient enrollment:

- Signed Research and Data Use Study Agreement
- Signed Conflict of Interest Statements
- Completed Delegation of Authority Log
- Signed and dated CVs for all staff on Delegation of Authority Log
- Ethics committee approval for protocol, informed consent document
- Study-specific training documents
- Other regulatory and training documentation may be required prior to site initiation

Prior to enrolling a patient, representatives from the DCC will conduct a site initiation for all investigators, coordinators, and any other health care professionals who may be involved in the study.

**Patient Confidentiality.**

All patients’ records will be kept confidential. Study Investigators, CAVI-J representatives may review source documentation as necessary, but all unique patient and hospital identifiers will be removed from source documents which are sent to the CAVI-J office. The aggregate data from this study may be published as per publication policy documented in this Protocol; however, no data with patient identifiers will be published.

**14. Statistical Plan**

**Sample size**

Sample size calculations: The relative risk of cerebrovascular event in patients with CAVI>10 has been estimated to be 1.73 compared with patients with CAVI ≤10; thus, the study enrolled 2.5 times as many patients with CAVI ≤10 as patients with CAVI>10, [19] in whom the risk of cerebrovascular events is anticipated to be 4.6% in 5 years [24]. From these data, the risks of cerebrovascular events in patients with CAVI ≤10 and CAVI>10 were anticipated to be 0.038 and 0.066 in 5 years, respectively. To detect this risk difference, the required sample size was calculated by Freedman’s method to be 810 for CAVI ≤10 and 2024 for CAVI >10 groups with a two-sided alpha of 5%, 80% power and 20% dropout rate [25]. On the basis of these assumptions, a sample size of 3000 was chosen for this study.

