**Figure S1 Competing Risk Analysis of Heart Failure-Related Hospitalization According to CAVI Tertiles**

[figure not shown]

*P* < 0.001

Cumulative incidence function curves illustrating the risk of heart failure hospitalization stratified by CAVI tertiles, with cardiovascular death treated as a competing event. A significantly higher cumulative incidence was observed in the high CAVI group (T3) (Gray’s test *P* < 0.001).

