**Table S1 Association of CAVI with heart failure-related hospitalization (Competing risk analysis)**

|  | Univariable | | |  | Multivariable* | | |
| --- | --- | --- | --- | --- | --- | --- | --- |
| CAVI | HR | 95%CI | P value |  | HR | 95%CI | P value |
| Primary outcome | |  |  |  |  |  |  |
| <8.0 | (reference) | | |  | (reference) | | |
| 8.0-9.0 | 3.041 | 0.615-15.03 | 0.170 |  | 3.100 | 0.682-14.130 | 0.140 |
| >9.0 | 6.289 | 1.427-27.71 | 0.015 |  | 6.436 | 1.472-28.380 | 0.013 |
| CAVI per 1 index | 1.591 | 1.188-2.131 | 0.002 |  | 1.573 | 1.156-2.141 | 0.004 |

*Adjusted for age, male sex

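### The 80% power holds only if 28.6% of patients have CAVI above 10; enrolment does not secure that share, the reported CAVI groups suggest less, and the analysis plan names no test at 10

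*Protocol*

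**What the plan says.** The Sample size paragraph (section 14) builds on a dichotomy at CAVI 10. The relative risk above 10 "has been estimated to be 1.73 compared with patients with CAVI ≤10". The split is given as a property of the study: "the study enrolled 2.5 times as many patients with CAVI ≤10 as patients with CAVI>10". The overall level comes from a cited source: "the risk of cerebrovascular events is anticipated to be 4.6% in 5 years". The two group risks "were anticipated to be 0.038 and 0.066 in 5 years, respectively". The calculation uses Freedman's method with a "two-sided alpha of 5%, 80% power and 20% dropout rate". It prints 810 patients for CAVI ≤10 and 2,024 for CAVI >10, and 3,000 is chosen.

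Section 7, Enrollment, says: "Consecutive consenting adult patients who meet the inclusion criteria and none of the exclusion criteria will be asked to participate in the study". The eligibility lists contain no CAVI criterion, and no quota or stratum by CAVI is set.

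The Analysis plan (section 14) foresees several CAVI groups, proportional hazards models and a cut-off found by ROC analysis. It names no comparison at 10.

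The supplement at the end of the document shows "Cumulative incidence function curves illustrating the risk of heart failure hospitalization stratified by CAVI tertiles" (Figure S1). Table S1 uses the groups <8.0, 8.0-9.0 and >9.0, and also a row for "CAVI per 1 index".

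**The concern.** In a cohort, the exposure split follows from who walks in. Power for a two-group comparison falls quickly as the smaller group shrinks, so a power statement tied to one split needs either a mechanism that delivers the split or a range around it. The protocol has neither. The only CAVI groups it reports have a middle band one unit wide ending at 9.0, which is hard to square with more than a quarter of patients above 10.

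At stake is what the 80% means. It belongs to a contrast that the Analysis plan never names, and it may not hold even for that contrast. A reader of a non-significant comparison at 10 could take the 80% as evidence against an association when the comparison had much less power.

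**Working it through.** **Inputs from the Sample size paragraph.** Two-sided 5%, 80% power, 20% dropout; relative risk 1.73 (0.066/0.038 = 1.737); overall 5-year risk 4.6%; φ = n(>10)/n(≤10) = 1/2.5 = 0.4, so the share above 10 is 1/3.5 = 28.6%. The split is a working input: (2.5 × 0.038 + 0.066)/3.5 = 0.046, the stated overall risk.

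**Reproducing the printed size.** Freedman: events = (1.960 + 0.842)² × [(1 + φ·HR)/(HR − 1)]² / φ.
- HR 1.73: 7.849 × (1.692/0.73)² / 0.4 = 105.4 events; /0.046 = 2,292; /0.8 = 2,865 (2,046 at ≤10, 818 above).
- HR 1.737: 103.8 events, giving 2,821 (2,015 and 806).

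The printed total is 810 + 2,024 = 2,834. It reproduces to within about 1%, but only with 2,024 as the ≤10 group. Taken as labelled, with 2.5 times as many above 10, Freedman gives 3,557 to 3,600. The labels are therefore reversed against the ratio in the same paragraph.

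**What share above 10 do the reported groups suggest?** Assume that 8.0 and 9.0 are the tertile limits. Then 28.6% above 10 needs 0.286/0.333 = 86% of the top third to exceed 10. For symmetric shapes the centre is 8.5 and the upper tertile lies 0.5 above it:
- Normal: SD = 0.5/0.4307 = 1.161; P(>10) = 1 − Φ(1.5/1.161) = 9.8%.
- Logistic: scale = 0.5/ln 2 = 0.721; P = 1/(1 + e^(1.5/0.721)) = 1/9 = 11.1%.
- Log-normal: mean of logs 2.138, SD 0.137; P = 1 − Φ(1.201) = 11.5%.
- Cauchy, an extreme heavy tail: scale 0.866; P = 1/6 = 16.7%.

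Rounding matters too. Limits of 7.95 and 9.05 give 12.0% under the normal, and unequal groups of 33/27/40% give about 17%.

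**Power by the protocol's own method.** N = 3,000 × 0.8 = 2,400. Power = Φ(z − 1.96), with z = √(d·φ) × 0.73/(1 + 1.73φ), where d is the number of events. Either the overall risk is held at 4.6% (d = 110.4) or the group risks are held at 0.038 and 0.066 (d falls with the share; 97.9 at 10%).

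| Share above 10 | Power, overall risk 4.6% | Power, group risks fixed |
|---|---|---|
| 28.6% | 82% | 82% |
| 20% | 76% | 74% |
| 16.7% | 72% | 69% |
| 15% | 69% | 66% |
| 11.5% | 62% | 57% |
| 10% | 57% | 52% |

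Example at 10%: φ = 0.111; √(110.4 × 0.111) = 3.50; × 0.73/1.192 = 2.145; Φ(0.185) = 57%. A simulated log-rank test with fixed group risks (4,000 runs, N 2,400) gave 82% at 28.6% and 53% at 10%. Reaching 80% at a 10% share would take about 5,700 to 5,800 patients by Freedman.

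**Continuous CAVI.** Under the normal shape, mean CAVI differs by 2.27 across the cut. If log hazard is linear in CAVI, the slope is ln(1.73)/2.27 = 0.241, or HR 1.27 per unit. Then z = √110.4 × 0.241 × 1.161 = 2.94 and power is 84%. A simulation at HR 1.285 per unit with the lower event count gave 82%. If risk instead only steps from 0.038 to 0.066 at 10, the per-unit test had about 24% power and the cut at 10 had 54%.

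**The case against.** The exposure split in a cohort is always assumed, and taking it from a cited earlier study is ordinary practice. The tertile limits are later results, whereas enrolment started in June 2013, so they could not have informed the sizing. Figure S1 speaks of tertiles without limits, and Table S1 gives limits without calling them tertiles. All of this stands. It means that the share above 10 can be given only as a range under stated assumptions, and that the planners are not shown to have ignored data they had. It does not remove the dependence of the 80% on one unsecured split, or the reversed labels.

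Three stronger readings are tempting.
- A reader might infer that power is only about 40%. That figure comes from Schoenfeld's formula at a 9.8% share. Schoenfeld gives 74% with the same inputs even at the planned split, so it is not comparable with a Freedman 80%.
- A reader might infer that the study is committed to an underpowered test at 10. The Analysis plan names no such test.
- A reader might infer that a per-unit test restores the power. That is true only if the effect is approximately log-linear.

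How CAVI enters the model may also be settled in an analysis plan not shown here, and Table S1 already has a per-unit row. Choosing the per-unit form after seeing results would be a data-driven choice.

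**Conclusion.** The concern holds in this limited form. The stated 80% is conditional on 28.6% of patients having CAVI above 10. Enrolment does not secure that share, and the power belongs to a contrast that the Analysis plan does not name. If 8.0 and 9.0 are the tertile limits, plausible shares are about 10 to 17%, and Freedman power is about 52 to 57% at 10%, 66 to 69% at 15% and 69 to 72% at 17%, against 82% as planned.

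This rests on reading Table S1's groups as the tertiles of Figure S1, on the shapes tried, on a relative risk of 1.73, and on N 3,000 less 20%. The documents do not establish a 10% share, because no mean, SD or count above 10 is given. The 4.6% risk is stated for cerebrovascular events, while the primary endpoint is cardiovascular death, myocardial infarction and stroke, so the event counts carry over only by assumption. The conditional nature of the 80% and the reversed labels need none of these assumptions.

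**What to change.** In the Sample size paragraph:
- State that the 80% holds only at the 2.5:1 split, and describe the split as an assumption rather than as something the study enrolled.
- Add Freedman power for shares above 10 from 10% to 30%.
- Swap the labels so that 2,024 belongs to CAVI ≤10 and 810 to CAVI >10.

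In the Analysis plan, name Cox regression on continuous CAVI (per 1 unit, two-sided 5%, with a spline check of linearity) as the main analysis of the primary endpoint, and keep >10 versus ≤10 as a secondary contrast. This fits the proportional hazards model already planned.

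The cost is wording and a less favourable power statement, with no extra patients. The per-unit test has about 82 to 84% power only under approximate log-linearity and if the 4.6% risk applies to the primary endpoint. It loses power if risk changes only at 10, and the spline check would reveal that but not recover the loss. If the choice is made after results are known, it must be labelled as post hoc. A range of shares is preferable to power at the observed share, which would be post hoc power.
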